**Fig. 1 Fig1:**
[figure not shown]
Study flowchart. Flowchart of planned participants’ selection and study design

The study is designed to detect a moderate effect size (d = 0.60, f = 0.35), as observed in the meta-analysis for CT for SAD with intense BE and prolonged sessions, as compared to CT with a reduced number of BEs and shortened sessions [7]. A power analysis with 90% power on a two-sided test where α = 0.05 revealed a sample size of *N* = 54 (27 per group). Based on data from previous studies [5], we expect a drop-out rate of 10%. Thus, 60 patients (30 per group) will have to be recruited.

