Standard CT comprises similar elements in the first and third stage of therapy; however, in the middle stage (stage 2), discussion techniques of challenging dysfunctional beliefs are used instead of BE. The techniques are described in detail in the previous manual [17] and include Socratic dialogue, the downward arrow technique, the prejudice technique, the life chart technique, positive data log, automatic thoughts protocol, and the pie chart technique. Dysfunctional beliefs associated with early experiences are identified and discussed. Homework mainly focuses on automatic thoughts and the practice of Socratic dialogue.

In standard CT, therapists are not encouraged to use BEs. Neither exposure based on a habituation rational nor formal social skills training is used.

To equalize therapists’ contact time and treatment dose, both treatments comprise the same amount of contact hours. In line with short-time-therapy in Germany, 25 units of 50-min duration are provided. In CT + BEs, up to eight sessions last 100 min due to the implementation of BEs. Standard CT includes one session of 100-min duration. Thus, the total number of sessions differs (17 vs. 25). The length of both treatments, however, is 6 months, since booster sessions are conducted (4-week interval) in the end of CT + BEs as prescribed in the manual.

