### Additional Assessments

For competence and adherence ratings, three videotapes will be selected: one from the initial stage (session 1, deriving the model) and two from the second stage (random selection from session 5–12). Session 1 is selected to cover general competencies such as guided discovery, whereas sessions from the second stage of treatment onwards are expected to refer to specific competencies (conducting BEs vs. cognitive restructuring). Competence and adherence will be rated by two independent, masked, and trained raters using the Cognitive Therapy Adherence Scale for Social Phobia (CTAS-SP) [18] the Cognitive Therapy Competence Scale for Social Phobia (CTCS-SP) [30]. The CTAS-SP comprises 17 items related to the specific interventions of CT, as described in the manual by Stangier et al. [17]. In the SOPHONET trial [6], a good interrater reliability (ICC = 0.87) was observed. Retest reliability was rtt = 0.90 for the total score and rtt = 0.28–1.0 for the individual items. Internal consistency was high (α = 0.99). Similarly, the psychometric properties of the 16-item CTCS-SP were good, with an interrater reliability of ICC = 0.81, retest reliability of rtt = 0.92, and an internal consistency of α = 0.97.

To assess the therapeutic relationship, the Helping Alliance Questionnaire (HAQ, patient and therapist version) will be used [31]. Both questionnaires will be administered at pre-treatment. The mean scores of the therapist and patient versions will be used to predict the outcomes.

Allegiance is assessed after the training and one pilot-therapy by the therapist version of the Reaction to Treatment Questionnaire developed by Holt & Heimberg [32]. For the purpose of the present study, two further items have been added to the scale referring to outcome expectations about specific intervention (BEs and cognitive restructuring).

As a predictor of treatment success, a 12-item version of the learning style inventory (Kolb LSI) will be administered at pre-treatment [33]. Based on previous treatment study results [34], it is hypothesized that the outcome of participants in the BE intervention will significantly predict an active experimentation learning style, whereas for participants in the standard CT (cognitive restructuring), the preferred learning style is predicted to be an abstract conceptualization learning style.

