### Statistical Analyses

Data will be analyzed with the SPSS statistical software package. All statistical analyses will be conducted on the intent-to-treat (ITT) sample and completer sample. Patients allocated to treatments will be classified as drop-outs if they miss more than 25% of the sessions. In the ITT analyses of treatment response, drop-outs will be considered as failures. In ITT analyses of dimensional measures, missing data will be replaced using the last observation carried forward approach for missing intervention- and post-assessments or follow-up observations. Analyses of the primary outcome measure (CGI-I), a categorical variable, will be conducted using χ^2^ or Fisher's exact tests. Dimensional measures will be submitted to analyses of covariance (ANCOVAs) in which pre-treatment scores will be controlled for. ANCOVAS will be performed separately for the post-treatment and 6-month follow-up assessments. Significance levels will be set at *p* < 0.05, two-tailed. Predictor analysis will be calculated by using logistic regression analysis with CGI-I as the dependent variable; independent variables are competencies, adherence, allegiance, and therapist-rated therapeutic relationships (therapist predictors), as well as patients’ preferred learning style at pre-treatment, changes in insight in SAD-related beliefs and cognitions, and patient-rated therapeutic relationships (patient predictors). Differences between treatments in the outcome predictions will be analyzed, with treatment interactions for each predictor. To test for possible therapist differences, a preliminary analysis of covariance will be conducted. As recommended, significance level in this case will be set at *p* < .30 [37]. If the effect is significant, a multilevel analysis using a mixed-model design is planned to include therapists as a random term [38]. A final analysis will be run to compare the pattern of results from both strategies of analysis taking possible therapist effects into consideration.

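### On the ITT sample, the drop-out and carry-forward rules can build the hypothesised association between insight change and response into the Hypothesis 4 regression

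*Protocol article*

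**What the plan says.** All of the rules involved stand in the protocol article, most of them in Statistical Analyses.

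- Scope: "All statistical analyses will be conducted on the intent-to-treat (ITT) sample and completer sample". The predictor regression is not exempted.
- Definition of drop-out: "Patients allocated to treatments will be classified as drop-outs if they miss more than 25% of the sessions". It rests on attendance, not on whether an outcome was obtained.
- Outcome rule: in ITT analyses of response, "drop-outs will be considered as failures".
- Missing-data rule: in ITT analyses of dimensional measures, missing values are replaced by LOCF.
- Model: "Predictor analysis will be calculated by using logistic regression analysis with CGI-I as the dependent variable". The independent variables include "changes in insight in SAD-related beliefs and cognitions, and patient-rated therapeutic relationships (patient predictors".

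Outcome Measures defines insight as the BABS total and schedules it at pre-treatment, post-treatment and 6-month follow-up, with nothing in between. Additional Assessments has the SCQ, the cognition measure, completed at every session. It takes competence and adherence from one session 1 tape and "two from the second stage (random selection from session 5–12". Selection of Patients says that people who discontinue are still asked to attend every assessment.

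**The concern.** Counting drop-outs as failures is a familiar convention when two arms are compared. Here the same convention fills the dependent variable of a regression while LOCF fills one of its predictors. For a drop-out with no post-treatment BABS, the last available value is the baseline, so the change is exactly zero, and the response is set to non-response. Neither value is measured.

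Hypothesis 4 expects that patients whose insight improves are more likely to respond. A cluster of patients placed at no change and no response pulls the regression in that direction whether or not the hypothesis is true. A significant insight predictor on the ITT sample could then be partly a product of the coding, and the article does not say which of the two samples governs Hypothesis 4.

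**Working it through.** **Inputs from the article.** Planned N is 60, of whom 54 are expected to remain. Design and Sample Size states "we expect a drop-out rate of 10" per cent. This reproduces: 54 / 0.90 = 60, and 0.10 × 60 = 6 drop-outs. The test level is two-sided 0.05.

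**Inputs assumed, because the article gives none.** Mean insight change (scored so that positive is improvement) of 0.5, 1.0 or 1.5 SD of the change score; response of 50% to 65% among the other 54 patients; and the number of drop-outs without a post-treatment BABS. Insight change and response are set to be independent among the 54, so any association found is spurious.

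**Step 1: who is a drop-out.** Treatments gives "Thus, the total number of sessions differs (17 vs. 25". 0.25 × 17 = 4.25, so 5 or more missed sessions (at most 12 attended). 0.25 × 25 = 6.25, so 7 or more missed (at most 18 attended). A late drop-out can therefore have both stage 2 tapes; one who leaves before session 5 has none.

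**Step 2: the induced difference, by hand.** Take 60% response among the 54 and a mean change of 1.0 SD, with all 6 drop-outs unassessed.

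- Responders: 0.60 × 54 = 32.4, mean change 1.00.
- Non-responders: 21.6 with mean 1.00, plus 6 at zero, gives 21.6 / 27.6 = 0.78.
- Induced difference: 1.00 − 0.78 = 0.22 SD, with no true association.

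With a within-group SD near 1, the log odds ratio per SD is close to this difference: exp(0.22) ≈ 1.25. The large-sample logistic fit gives odds ratios of 1.13, 1.25 and 1.36 at 0.5, 1.0 and 1.5 SD.

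If 3 of the 6 are assessed and have the same mean change as the others, the non-responder mean is (21.6 + 3) / 27.6 = 0.89, and the induced difference halves to 0.11 SD.

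**Step 3: false-positive rate.** Single-predictor logistic regression, simulated with 1,500 to 8,000 runs per setting. The second column spans response of 50% to 65% and Wald and likelihood-ratio tests. The third gives 50% / 65% response with the Wald test.

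| Assumed mean change | All 6 unassessed | 3 of 6 assessed, still coded failures |
|---|---|---|
| 0.5 SD | 5% to 8% | 4.7% / 4.8% |
| 1.0 SD | 9% to 13% | 5.7% / 5.8% |
| 1.5 SD | 14% to 24% | 6.3% / 8.8% |

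A repeat of the half-assessed case gave 4% to 8%, so its overall range is 4% to 9%, with spurious odds ratios of 1.06 to 1.19. With 4 of 6 assessed the rate is 4% to 6%. With the drop-outs left out it is 5% to 6%, which is nominal within simulation error. With all 6 unassessed, 98% to 100% of false positives at 1.0 SD or more lie in the hypothesised direction, and 87% to 92% at 0.5 SD.

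**The case against.** Several objections have force.

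- **The reading is inferred.** The LOCF sentence concerns ITT analyses of dimensional measures, which the article then sends to ANCOVA. Its use for a covariate in the logistic model is not stated. This stands as a caveat, but the scope sentence covers all analyses and the BABS is a dimensional measure, so it is the natural reading. The point also does not rest on an omission that a fuller document would fill: it follows from rules the article states.
- **Discontinued patients will be assessed.** The article seeks this, and it cuts the inflation sharply, as the third column of the table shows. A drop-out with an observed BABS keeps the real change but is still forced to failure, which can weaken the association rather than create it.
- **The completer analysis is free of the artefact.** This is correct, and it limits the harm.
- **The forced pair may not enter a joint model.** If all predictors are fitted together and patients without stage 2 tapes are deleted, an early leaver contributes nothing. The rates above therefore apply only to drop-outs who do enter the model.

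A reader might also infer that drop-outs cannot be scored at all, or that losing early leavers for lack of stage 2 tapes biases the competence and adherence results. The documents support neither. Outcome and insight change do receive values. Learning style and the alliance questionnaire are taken before treatment, and allegiance is a therapist measure taken after training and a pilot therapy. Only the stage 2 tape scores of early leavers are unavailable. As for bias, selection that depends on the outcome alone shifts the intercept of a logistic model, not its slopes, so none has been shown.

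**Conclusion.** The point holds in a narrow form. On the natural reading, the stated rules build a positive association between BABS change and response into the ITT version of the Hypothesis 4 regression, through drop-outs who lack a post-treatment BABS. The inflation is negligible to modest if half of the drop-outs are assessed, and reaches 14% to 24% only if all 6 are unassessed, all enter the model and mean insight change is as large as 1.5 SD. The mean change, the response rate and the number unassessed are assumptions.

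It would be wrong to extend this to every change predictor. SCQ change is measured at each session, so carrying it forward does not force it to zero. The pre-treatment predictors are not affected, nor is the primary comparison of responder rates. Hypothesis 4 is an additional objective, so this is a correction worth making and not a threat to the trial's main result.

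**What to change.** Add a sentence to Statistical Analyses that exempts the predictor regression from the failure and LOCF rules. Run it on all randomised patients with an observed CGI-I rating and an observed BABS change, including assessed drop-outs with their actual rating. Alternatively, multiply impute outcome and predictors jointly.

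Report how many patients lack a rating and how many lack stage 2 tapes. Do not substitute the session 1 tape score for missing stage 2 scores: Additional Assessments says that the first covers general competencies and the later tapes specific ones.

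The cost is one sentence and, with the observed-data option, up to about 6 fewer patients in an analysis that is not the primary one.

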### Hypotheses

The present study aims to investigate whether the enhanced implementation of BEs will improve the efficacy of CT for SAD. This goal will be achieved by the following measures:
comprehensive training of the therapists’ competencies in conducting in-session BEs, including self-practice and self-reflection,encouraging therapists to implement this intervention as the major component of the treatment in continuous supervision,establishing double hour sessions to ensure an appropriate setting for BEs.

The experimental condition (CT plus enhanced BEs) will be compared to standard CT as the control condition. An active control condition has been chosen as comparator to control for specific effects of conventional components of cognitive therapy. In standard CT, therapists’ training, supervision, and settings are arranged with a focus on traditional cognitive restructuring techniques.

In a randomized controlled trial, the following major hypothesis will be tested:*Hypothesis 1: As compared to standard CT, CT plus enhanced BEs will result in a significantly higher rate of responders at (a) post-treatment and (b) follow-up.*

The secondary objective is to identify differences in the process of therapy and their association with treatment outcomes. The process-related variables to be assessed include the following therapist variables: general and treatment-specific competencies, and adherence to and allegiance with the treatment manual. The patient variables and treatment outcomes are: changes in insight in SAD-related beliefs, cognitions, avoidance, and symptoms, as well as comorbid depressive symptoms.*Hypothesis 2: In the CT plus enhanced BEs, as compared to standard CT, therapists will show higher levels of adherence related to BEs, and significantly higher levels of allegiance with the treatment approach.**Hypothesis 3: In CT plus enhanced BEs, as compared to standard CT, changes in SAD-related insights, cognitions, avoidance, and symptoms (a) from baseline to post-treatment, and (b) from baseline to follow-up will be significantly increased.*

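### The Hypothesis 4 logistic regression names no treatment main effect, so coefficients for predictors that the trial expects to differ by arm could partly reflect the treatment difference

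*Protocol article*

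**What the plan says.** The model is in the protocol article, Statistical Analyses: "Predictor analysis will be calculated by using logistic regression analysis with CGI-I as the dependent variable". Two groups of independent variables follow. The first group: "independent variables are competencies, adherence, allegiance, and therapist-rated therapeutic relationships (therapist predictors"). The second is patients' preferred learning style together with "changes in insight in SAD-related beliefs and cognitions, and patient-rated therapeutic relationships (patient predictors"). Counting insight change and cognition change separately, there are four variables in each group and eight in all. Treatment is not one of them.

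The next sentence brings treatment in: "Differences between treatments in the outcome predictions will be analyzed, with treatment interactions for each predictor". It does not say whether this is the same model or a second one, and it does not name a treatment main effect.

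The Hypotheses section sets out the arm differences that the trial expects:
- Hypothesis 1, response: "CT plus enhanced BEs will result in a significantly higher rate of responders".
- Hypothesis 2, therapist variables: "therapists will show higher levels of adherence related to BEs, and significantly higher levels of allegiance with the treatment approach".
- Hypothesis 3: "changes in SAD-related insights, cognitions, avoidance, and symptoms" are expected to improve more in CT plus BEs.

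Hypothesis 4 then expects adherence, allegiance, and insight and cognition change, among others, to predict a positive outcome.

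**The concern.** By the trial's own hypotheses, arm acts on both sides of this regression: it raises response, and it raises several of the predictors. In a pooled model without an arm term, a variable that is higher in the arm with more responders is associated with response even if it has no relation to response inside either arm. Success on Hypotheses 1 to 3 would then push Hypothesis 4 towards confirmation. The trial could report that allegiance or belief change predicts outcome when part or all of that association is the treatment difference seen again. The bias in the coefficient does not shrink as the sample grows.

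This matters most for allegiance. The Discussion treats it as a rival explanation for the effects of psychological treatments, and therapists are randomised to one arm only. A pooled allegiance coefficient cannot separate allegiance from treatment.

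**Working it through.** The plan gives no figure of its own for this analysis, so there is none to reproduce.

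**Inputs from the article:** 60 patients, 30 per group; design effect d = 0.60 (Design and Sample Size); two-tailed 0.05 (Statistical Analyses); eight predictors.

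**Assumptions, not in the article:** control response 50%; predictors normal with within-arm SD 1 and arm gap g; no within-arm relation between predictor and response; each predictor varies from patient to patient.

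**Response in the other arm.** Converting d to an odds ratio: exp(0.60 × π/√3) = exp(1.088) = 2.97. Control odds are 1, so the other arm has 2.97/3.97 = 0.748, about 75%.

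**Why the pooled association is not zero.** With equal arms, Cov(X, Y) = within-arm covariance + ¼ × g × (p1 − p0) = 0 + ¼ × g × 0.25. The variances are Var(X) = 1 + g²/4 and, with overall response 0.625, Var(Y) = 0.625 × 0.375 = 0.234.

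**Hand approximation.** r = Cov/√(Var X × Var Y), z = r√60, false-positive rate = P(|N(z,1)| > 1.96):

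| Gap g | Cov | r | z | Rate |
|---|---|---|---|---|
| 0.6 | 0.0375 | 0.074 | 0.57 | 9% |
| 1.0 | 0.0625 | 0.115 | 0.89 | 15% |
| 1.5 | 0.0938 | 0.155 | 1.20 | 22% |
| 2.0 | 0.1250 | 0.183 | 1.41 | 29% |

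**Simulated logistic regressions** (Wald test, n = 60, 2,000 to 3,000 runs per setting; ranges cover separate runs):

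| Model | Gap | Without arm | With arm |
|---|---|---|---|
| One predictor | 0.5 SD | 7% | about 4% |
| One predictor | 0.6 SD | about 8% | 4% |
| One predictor | 1.0 SD | 11–12% | 4–5% |
| One predictor | 1.5 SD | 20–21% | 4–5% |
| One predictor | 2.0 SD | 27–29% | 4–5% |
| Eight predictors, three shifted, rate per predictor | 0.6–2 SD | about 9–10% | about 6% |
| Eight predictors, two shifted, rate per predictor | 0.5–1.5 SD | 7–14% | 5–6% |
| Eight predictors, four shifted, rate per predictor | 0.5–1.5 SD | 7–9% | 5–6.5% |

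The hand approximation and the simulation agree to within a few points. Without arm, the spurious large-sample odds ratio is 1.25 to 1.31 per SD for gaps of 1 to 2 SD. With arm, the median coefficient returns to about 0.

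In the eight-predictor model with three shifted, at least one of the three is significant in 23.5% of trials without arm against 16.0% with arm at 0.6 SD. For 1–2 SD the figures are 25–28% against 16–17%. The excess attributable to omitting arm is thus roughly 7 to 12 points.

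**Interaction step, one predictor, gaps 0.5, 1.0 and 1.5 SD.** With a treatment main effect, the predictor term is falsely significant in 3.4–3.8% of runs and the interaction in 4.6–5.1%. Without it, the interaction term itself rises to 7.4%, 12.1% and 14.9%. The second step therefore depends on the main effect as well.

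**The case against.** The strongest reply is that treatment is not absent from the predictor analysis. The sentence after the list plans an interaction with treatment for every predictor, and Additional Assessments makes arm-specific predictions about learning style that cannot be tested without arm. Interaction models normally carry both main effects, and a condensed article need not say so. If they do here, the predictor effects in those models are within-arm and the problem is gone from that step. This stands, and it rules out a reading that a reader might infer: that the plan ignores treatment, or that arm differences are bound to make allegiance and belief change look like predictors. Yet the article states the variable list for the main regression, and treatment is not on it. The interaction sentence addresses a different question: whether prediction differs between arms.

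Size is the second objection. No passage supports arm gaps of 1 to 2 SD. The Discussion describes measures to keep allegiance balanced, and at 0.6 SD the inflation is only a few points. This also stands. When several shifted predictors share the arm signal, the rate per predictor stays near 10%.

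Third, competence, allegiance and belief change are presented as the route by which enhanced training works, so the between-arm component could be argued to belong to the question. This does not rescue the model, because the outcome model for a mediator also needs treatment in it.

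Finally, allegiance is assessed per therapist and therapists are nested in arm. Simulations that vary it by patient do not give its exact error rate.

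**Conclusion.** The point holds in a limited form. The listed regression omits treatment, and the plan does not say that a treatment main effect accompanies the predictors or their interactions. Given Hypotheses 1 to 3, the pooled coefficients for allegiance, adherence, and insight and cognition change could partly reflect the treatment difference, in the direction that favours Hypothesis 4.

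Under the stated assumptions the inflation is moderate: small at a gap equal to the design effect, substantial only for single-predictor models with gaps of 1.5 SD or more. Both the gaps and the 50% control rate are assumptions. The documents do not support saying that false predictors would generally emerge: at 0.6 SD, none of the three shifted predictors is significant in 76.5% of simulated eight-predictor trials (100 − 23.5).

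Hypothesis 4 is an additional objective, and the tests of Hypotheses 1 to 3 are unaffected. The change is still worth making, because it is cheap and settles what the coefficients mean.

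**What to change.** Add one sentence to Statistical Analyses: the treatment main effect is a covariate in every Hypothesis 4 model, including each model with treatment-by-predictor interactions. In the models without interactions, each predictor coefficient is then a within-arm association, which is what Hypothesis 4 needs. Centring predictors at their arm means is not required for this, since the slope is the same once arm is in the model.

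The cost is one degree of freedom per model and no new data. Precision for allegiance will fall, because within an arm it varies only between therapists. The report should say that a weak allegiance result may reflect that limited variation.

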### Treatments

In the study, two conditions, CT plus enhanced BEs vs. standard CT, are compared; these use different interventions in the middle stage of treatment to achieve a change in SAD-related cognitions:
behavioral experimentstraditional (verbal) methods of cognitive restructuring.

CT based upon the Clark & Wells model pursues two primary goals:
to reverse the processes that maintain SAD (self-focused attention, distorted images of the social self, and safety behaviors), andto disconfirm dysfunctional beliefs (using BE, imagery rescripting, and cognitive restructuring).

As described in detail in the revised manual [16], the treatment comprises the following interventions:
Stage 1 (sessions 1–3): deriving an individual cognitive model, experiential exercises to avoid self-focused attention and safety behaviors, providing video feedback, and enhancing attention training;Stage 2 (sessions 4–13): BEs (in-session and homework) to test dysfunctional beliefs, and imagery rescripting to modify maladaptive beliefs linked to recurrent negative imagery;Stage 3 (14–17): termination of treatment (blueprint of techniques helpful for relapse prevention) and booster session.

To implement BEs, prolonged sessions are required to prepare the experiment, including defining the expectations to be tested, outlining the behaviors to be enacted in the experiment, and choosing an appropriate situation outside the therapy room. Thus, 2 × 50 min will be scheduled as the standard duration of the session.

Furthermore, guided discovery and standard CT discussion techniques are used in stage 2 to support the reflection of BEs consequences. However, no automatic thoughts records are used, and verbal techniques of cognitive restructuring are embedded in the planning of BEs and the analysis of the results. In contrast to standard CT, therapists will use the Social Cognitions Questionnaire (SCQ) on a weekly basis to determine the focus of the therapy.

As in standard CT, neither exposure based on a rational habituation nor formal social skills training is used.

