The SCQ (Social Cognition Questionnaire) [35] (German translation [36]) is a self-report measure to assess the frequency and intensity of SAD-related cognitions. The questionnaire will be completed by the patients at every session.

Detailed procedure of the measurements is listed in the schedule of enrolment, interventions and assessments (Fig. 2).

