## Discussion

This study is the first to determine the efficacy of BE as a component of CT. Several previous studies have shown the overall efficacy of CT including BE [7], but the incremental efficacy of BE as an additive intervention has yet to be verified. BEs imply exposure to critical social situation, but not with the explicit goal of achieving habituation; rather, it is to test dysfunctional beliefs [39]. Thus, BEs go beyond traditional verbal methods of cognitive restructuring, including both Socratic dialogue and the automatic thoughts questionnaire, which involve the logical disputation of dysfunctional beliefs and aim to provide insight. BEs, however, by approaching critical and frequently avoided social situations, are suggested to provide information challenging dysfunctional beliefs. Thus, in contrast to traditional exposure, BEs explicitly refer to cognitive mechanisms; in particular, encoding new information into memory [40]. Although traditional exposure may implicitly involve similar mechanisms, BEs not only aim to change dysfunctional beliefs, but in addition target the modification of the cognitive processes that maintain them, i.e., self-focused attention, as well as safety behaviors and distorted images [41]. The results of a recent meta-analysis [10] indicate that BEs might be superior to exposure in some anxiety disorders, among them SAD; however, the results do not clarify whether BEs contribute significantly to the efficacy of CT in general. Furthermore, the superiority of the behavioral experiment condition in this review could possibly reflect therapeutic-allegiance effects since most of the research groups did have recognized allegiance to CT. Therapeutic allegiance, however, improves the outcome of treatment and may place treatment conditions with higher allegiance in a more favorable position compared to competing treatment conditions.

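### The Hypothesis 4 regression enters changes in insight and cognitions beside the therapist predictors, so on its plain reading it attenuates the therapist associations it is meant to test

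*Protocol article*

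**What the plan says.** The Statistical Analyses section states: "Predictor analysis will be calculated by using logistic regression analysis with CGI-I as the dependent variable". The list that follows begins "independent variables are competencies, adherence, allegiance, and therapist-rated therapeutic relationships (therapist predictors" and continues, after learning style, with "changes in insight in SAD-related beliefs and cognitions, and patient-rated therapeutic relationships (patient predictors". It adds treatment interactions for each predictor. It names no blocks, order of entry, separate models or mediation step.

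Elsewhere the article gives the change variables another role:

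- Hypotheses: "The patient variables and treatment outcomes are: changes in insight in SAD-related beliefs, cognitions, avoidance, and symptoms". Hypothesis 3 then tests these changes as effects of treatment, from baseline to post-treatment and to follow-up.
- Treatments: one of the two primary goals of therapy is to "disconfirm dysfunctional beliefs (using BE, imagery rescripting, and cognitive restructuring".
- Discussion: behavioral experiments, by approaching feared situations, "are suggested to provide information challenging dysfunctional beliefs".
- Outcome Measures: change in insight (BABS) runs from baseline to post-treatment and follow-up, the visits at which CGI-I is rated.

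Competence and adherence are rated on a session 1 tape and "two from the second stage (random selection from session 5–12" (Additional Assessments). Allegiance is measured after training and one pilot therapy. Hypothesis 4 expects competencies, adherence and allegiance to predict good outcome.

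**The concern.** Hypothesis 4 asks whether patients do better when their therapists are more competent, adherent or committed to the approach. A model that also holds belief and cognition change fixed asks something narrower: whether these therapist variables matter among patients whose beliefs changed equally. If good technique works partly by changing beliefs, as the protocol says, the second question removes part of the answer to the first.

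A null therapist coefficient would then be ambiguous. It could mean that competence does not matter, or that it works through beliefs as theorised. The Background cites a competence-outcome correlation of 0.28 as part of the case for more intensive training, so the distinction matters for how this analysis is read.

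**Working it through.** **Plan's own figure.** None is given for this regression, so there is nothing to reproduce.

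**Inputs from the article.** n = 60 (Design and Sample Size); two-sided 0.05 (Statistical Analyses); competence-outcome correlation r = 0.28, from an earlier German trial (Background).

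**Assumed inputs.** The path a from therapist variable to belief change; the share m of the therapist effect that runs through that change; the response rate. Each simulation uses one therapist variable and one change score, which is simpler than the planned model.

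**Formula.** Let A be the therapist variable, M the change score and L the latent outcome, all standardised:

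- M = a·A + noise
- L = c·A + b·M + noise, with b = m·r/a and c = (1 − m)·r

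Without M, the coefficient of A is c + a·b = r = 0.28. With M, it is c = (1 − m)·0.28: 0.14 at half mediation, 0.07 at three quarters and 0 at full mediation. Example with a = 0.4 and m = 0.5: b = 0.14/0.4 = 0.35, and 0.14 + 0.4 × 0.35 = 0.28.

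**Set-up 1.** Logistic regression, n = 60, 1500 runs per setting, a = 0.4 or 0.5, 50% response:

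| Share mediated | OR per SD of A, without M | OR with M | Power without M | Power with M |
|---|---|---|---|---|
| 0% | 1.62 | 1.62-1.65 | 38-40% | 29-34% |
| 50% | 1.59-1.63 | 1.29 | 38-39% | 11-12% |
| 75% | 1.59-1.62 | 1.12-1.15 | 37-39% | 6% |
| 100% | 1.62 | 0.98-1.00 | 39-40% | 4-5% |

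At n = 2000 the odds ratios are the same: about 1.6 without M; with M, 1.28-1.29, 1.13-1.14 and 0.99-1.01 at 50%, 75% and 100%. The log odds ratios follow the formula: ln 1.29 / ln 1.6 = 0.255/0.470 = 0.54, close to 1 − 0.5. The loss is therefore a change in what is estimated, not small-sample noise.

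**Set-up 2.** n = 60, 55% response, change score measured with reliability 0.8, change-outcome correlation 0.7. Power is about 39-40% without the change score and 5-7% with it at full mediation. At half mediation it is 36-38% without and 18-20% with.

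**Would adjusting for early cognition change be a safe substitute?** The SCQ is recorded often ("The questionnaire will be completed by the patients at every session"), so change before the first stage 2 tape might be used. In set-up 2 this keeps power at 43-44% if the therapist variable acts only on later change. If it acts on early change, power falls from 38-39% to 6%. If it acts on both, power falls from 36% to 15-18%. Session 1 ratings and allegiance come before early SCQ change, so for them that adjustment can remove a real effect in the same way.

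**The case against.** **The article never says that all terms enter together.** It labels two sets, therapist and patient predictors, and a fuller plan might fit them separately. This stands as a caveat. A single list of independent variables for one regression is still most plainly read as one model, and nothing in the text separates the sets.

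**Unique prediction is a legitimate question, and Hypothesis 4 names the change scores as predictors.** True, but it also expects the therapist variables to predict outcome, and the joint model does not answer that.

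**The therapist effect need not vanish.** A reader might infer that it is adjusted away altogether. The documents do not support this. Treatments gives a separate first goal (self-focused attention, distorted self-images, safety behaviors), and the Discussion says behavioral experiments target these processes as well as beliefs. By the protocol's own account mediation is partial.

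**The window for cognition change is not fixed.** Statistical Analyses gives none. The whole-treatment window comes from Hypothesis 3 and is explicit only for insight. This stands.

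**Stage 2 ratings could reflect earlier improvement.** A reader might go further and infer that one-predictor models are confounded and must be adjusted for early SCQ change. Nothing in the documents says that improved patients are rated as better treated, and any size for such a link is assumed. The adjustment can also remove real effects, as shown above. The possibility merits a stated limitation, not a rule.

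**Conclusion.** The point holds in limited form. On the plain reading of one joint model, the therapist coefficients for Hypothesis 4 estimate only the association that bypasses belief and cognition change, and they are attenuated toward zero. With n = 60 and r = 0.28, power for a single therapist predictor goes from about 36-40% to about 11-20% at half mediation and about 4-7% at full mediation. The mediated share, path strengths and response rate are assumptions, and the document does not allow the actual attenuation to be computed.

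Three stronger conclusions do not follow. The effect is not shown to be removed entirely. Confounding of the stage 2 ratings is possible but not documented. The trial's main conclusion is not at risk, because it rests on the randomized comparison in Hypothesis 1, whereas Hypothesis 4 serves an additional objective. The correction is still worth making, because it is cheap and leaves a null result easier to interpret.

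**What to change.** In Statistical Analyses, state that the therapist-predictor model for Hypothesis 4 is fitted without changes in insight and cognitions. Report those changes in a separate second step, labelled as a possible pathway from therapist behaviour to outcome and not as competing predictors. State the time window used for cognition change.

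Do not make adjustment for early SCQ change the rule. Add one sentence of limitation: competence and adherence ratings from sessions 5-12 could partly reflect improvement that had already occurred.

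Cost: a few lines of text, with no new data and no further patients. The small downside is that the change scores are no longer tested head to head with the therapist variables in one model. The change does not make the analysis well powered: under these assumptions, power for a real effect of r = 0.28 is still only about 40%.
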